A key advantage of VR, as compared to other interactive modalities for assessing substance use risk [20], is its capacity for synchronized tracking of behavioral and physiological responses during immersive cue exposure. Existing research has shown that nicotine-related cues, whether physical (eg, cigarette packaging) or virtual (eg, images or videos), can elicit stronger emotional and behavioral responses in cigarette smokers than in nonsmokers [21,22]. Metrics such as attentional bias (measured via eye tracking) and autonomic arousal (eg, heart rate [HR] and electrodermal activity [EDA]) capture implicit and automatic processes that may reveal cue reactivity, substance use tendencies, and motivation to consume nicotine [23]. These biometric responses may address important limitations of existing measures of risk, as most rely on self-report, are prone to social desirability and recall bias, and have limited sensitivity to real-time emotional and cognitive processes underlying addiction [8,24]. Furthermore, VR-elicited biometrics may provide an alternative to biological specimens by serving as noninvasive biomarkers for vaping and nicotine use [25]. Together, VR-based psychophysiological methods may serve as valid and acceptable objective tools for identifying nicotine use and predicting addiction risk.

However, despite the use of VR to study cigarette smoking cue reactivity, little work has examined whether VR can distinguish current and future nicotine vaping behaviors. To date, studies have largely used cigarette smoking cue environments to differentiate individuals based on psychophysiological responses using single modalities such as electroencephalogram and eye-tracking [17,26]. Furthermore, no current work has combined multimodal physiological data (eg, visual attention and physiological arousal) with psychological measures (eg, impulsivity, craving, and motivation to quit) to model individuals’ intentions to initiate or cease vaping. Such predictive modeling could play a crucial and timely role in identifying at-risk individuals early and tailoring interventions accordingly.

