### Study Population and Study Flow

This study will recruit young adults aged 18 to 21 years living in or around New Haven, Connecticut. Recruitment efforts will focus on two distinct groups: (1) individuals who currently use nicotine-containing e-cigarettes, defined as use on 10 days or more within the past 30 days (*vapers*), and (2) individuals who report never having used nicotine-containing vapes (*nonvapers*). Participants who use nicotine in non–e-cigarette forms (eg, cigarettes and nicotine pouches) will not be excluded but will be assessed at baseline so that such exposure can be accounted for analytically. This design allows the comparison of psychophysiological cue reactivity between vapers and nonvapers, as well as the exploration of predictors of future initiation risk among nonvapers.

Eligibility will require participants to be fluent in English and able to provide informed consent. Exclusion criteria include self-reported photosensitive epilepsy, significant visual, hearing, or mobility impairment, current or recent (past 30 days) use of cannabis-containing e-cigarettes, current use of other illicit substances (eg, 3,4-methylenedioxymethamphetamine or ecstasy, and methamphetamine), nonmedical misuse of prescription drugs, or reliance on eyeglasses that are incompatible with VR eye-tracking hardware. These exclusions help reduce noise in psychophysiological responses that may arise from nonnicotine substances, ensuring clearer differentiation between the study groups. A total sample of 40 participants will be enrolled, which is sufficient for detecting medium group effects in VR cue-reactivity studies while accounting for potential data loss.

The study flow is shown in Figure 1. Eligible participants will complete a single laboratory session lasting approximately 1 hour. After providing informed consent and completing baseline questionnaires, participants will be fitted with a VR headset and biometric sensors. They will complete 3 VR scenes: a neutral baseline, a vaping cue scene without social pressure, and a vaping cue scene with social pressure in a counterbalanced order. Physiological data will be recorded continuously, and brief self-report measures (craving, presence, and social presence) will follow each cue scene. Participants will rate the system’s usability after finishing all the VR sessions. The session will conclude with a short semistructured interview, debriefing, and compensation.

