After each VR cue scene, participants will remove the headset and complete part 2 of the assessment questionnaire. Part 2 contains self-report measures on craving, presence, social presence, and system usability. An overview of the assessment used in the laboratory visit is listed in Table 2.

**Table 2. T2:** Post–VR cue exposure measures assessing craving, presence, social presence, and system usability.

Measures	Items	Response options
Measured twice, after each VR cue scene		
Craving for vaping or smoking e-cigarettes Visual Analog Scale (VAS) [47]	1 item: “I have a desire for vaping/having an e-cigarette right now.”	A visual scale, ranging from 0 (“Not at all”) to 100 (“Extremely”)
Adapted presence and social presence questionnaire from *Presence (IPQ)* and *Social Presence by Networked Minds Measure of Social Presence* [48,49]	1 item from IPQ measuring general presence: “In the computer-generated world I had a sense of ‘being there’” (general presence item from IPQ). 6 items from the co-presence subscale (*α*=0.84). An example is: “The virtual humans caught my attention.”	5-point Likert scale, ranging from (0) “Do not agree at all” to (4) “Very Likely”
Measured once, after all VR scenes		
System usability by V*irtual Reality System Usability Questionnaire (VRSUQ)* [50]	9 items (*α*=0.679‐0.896). An example is: “The system responded well to my manipulations as expected with no delays.”	5-point Likert scale, ranging from (1) “Strongly disagree” to (5) “Strongly agree”

Eye gaze and physiological data will be recorded continuously during both VR cue scenes as follows:

Eye-gaze behavior: raw eye-tracking data and gaze fixations on predefined regions of interest (eg, vaping-related cues) will be collected and processed into fixation-related metrics such as fixation count, duration, and dwell time.HR and heart rate variability (HRV) will be monitored as indicators of autonomic arousal. HRV will be further processed into standard time-domain metrics, including the root mean square of successive differences, which reflects short-term parasympathetic activity, as well as frequency-domain metrics such as the low-frequency–to–high-frequency ratio, commonly interpreted as an index of sympathovagal balance [51].EDA will also be recorded to measure autonomic arousal and decomposed into tonic skin conductance levels and phasic SCRs using continuous decomposition analysis [52].

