##### Secondary Analyses

For the secondary objective, we will assess associations between multimodal physiological measures and subjective vaping-related outcomes. Correlation and regression analyses will first be conducted to examine pairwise relationships among eye-gaze metrics (eg, total fixations and mean fixation duration), HR, EDA, and subjective measures (eg, craving, dependence scores, and motivation to quit or susceptibility to initiate use). Depending on data distribution, the Pearson or Spearman correlations will be used. Partial correlations or multiple regression models will account for potential covariates such as age, gender, and other substance use.

To further explore multivariate relationships between physiological responses and vaping-related outcomes, exploratory regularized regression analyses will be conducted. Given the pilot sample size, we will use regularized logistic regression with the least absolute shrinkage and selection operator to examine whether aggregated physiological and subjective measures are associated with vaping status (vaper vs nonvaper). Candidate predictors will include summary features derived from eye-gaze behavior (eg, fixation count, proportion of fixation duration on vaping-related cues, and time to first fixation), HRV metrics derived from photoplethysmography signals (including time-domain indices such as root mean square of successive differences and frequency-domain measures such as low-frequency to high-frequency ratio), EDA (eg, mean number of SCRs, mean SCR amplitude, and mean skin conductance level), and relevant subjective responses (eg, craving, presence, and social presence).

Physiological signals will undergo standard preprocessing procedures, including signal quality checks, removal of segments affected by motion artifacts or signal instability, and aggregation into scene-level summary features. Participants will be excluded if more than 15% of their physiological data is missing, and EDA signals will be removed if more than 15% of values are zero or negative, indicating poor sensor contact [56,57]. The regularization parameter will be selected using cross-validation to reduce overfitting [58]. Given the exploratory nature of this analysis and the modest sample size, findings will be interpreted cautiously and used to identify candidate multimodal markers for future confirmatory studies rather than to develop generalizable prediction models.

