### Conclusions

This protocol describes a pilot study that integrates VR with multimodal psychophysiological assessment to examine vaping cue reactivity among young adults. By combining eye-tracking, HR, EDA, and self-report measures within bespoke VR environments, this study aims to establish the feasibility of VR-based biomarkers in distinguishing vaping status and modeling vaping-related intentions and susceptibility. The findings will guide the development and evaluation of scalable, noninvasive VR tools for identifying early markers of nicotine use risk. This work also lays the groundwork for extending and testing the approach with younger adolescents, with the long-term goal of supporting early detection and prevention of nicotine addiction and initiation.

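### The vaping-status LASSO pools self-reported craving with the biometric features and names no physiology-only or subjective-only model, so it does not isolate what the biometrics contribute

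*Protocol article*

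**What the plan says.** Secondary Analyses describes a regularized logistic regression with LASSO "to examine whether aggregated physiological and subjective measures are associated with vaping status (vaper vs nonvaper"). The candidate list names eight physiological examples: three gaze features, two heart rate variability indices and three electrodermal features. In the same list stand "relevant subjective responses (eg, craving, presence, and social presence"). The penalty is chosen by cross-validation. Findings are to be read cautiously, as candidate markers for later confirmatory work and not as a generalizable prediction model.

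The craving measure in Table 2 is a single 0 to 100 rating of "I have a desire for vaping/having an e-cigarette right now". Under Study Population and Study Flow, vapers are current users, "defined as use on 10 days or more within the past 30 days", and nonvapers are "individuals who report never having used nicotine-containing vapes".

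The aim is put in two ways. The Abstract objective and the Secondary Aim ask about subjective and physiological measures in combination. The Background presents biometrics as an answer to the limits of self-report, says that "VR-elicited biometrics may provide an alternative to biological specimens by serving as noninvasive biomarkers for vaping and nicotine use", and closes by asking whether psychophysiological responses can tell vaping status apart. The Conclusions state that "this study aims to establish the feasibility of VR-based biomarkers in distinguishing vaping status".

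**The concern.** A rating of desire to vape is close in content to the variable that defines the groups. If it discriminates strongly, a LASSO containing it will perform well whatever the sensors record. Good performance from such a model could then be taken as support for multimodal biomarkers when one self-report item produced it, which is the kind of measure the biometrics are meant to improve on.

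The model's narrower use, picking candidate markers, could suffer too. When one predictor carries most of the signal, the cross-validated penalty is tuned largely to that predictor, and the sorting of physiological features into informative and uninformative becomes less clean.

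**Working it through.** **The plan's own figure.** The only computed figure is the sample size, and it does not concern the LASSO. For the group × cue interaction, λ = f²·N·m/(1 − r) = 0.0625 × 34 × 2/0.5 = 8.5, with 1 and 32 degrees of freedom. At α = 0.05 (assumed; not stated) power is 0.807, and N = 32 gives 0.781. The stated minimum of 34 is reproduced. What carries over is the planned 20 versus 20.

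**How strong must craving be?** The article gives direction only (Primary Aim). For normal scores with equal variance, AUC = Φ(d/√2):

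| Assumed craving d | 0.5 | 0.8 | 1.0 | 1.5 | 2.0 | 2.5 | 3.0 |
|---|---|---|---|---|---|---|---|
| Craving-only AUC | 0.64 | 0.71 | 0.76 | 0.86 | 0.92 | 0.96 | 0.98 |

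Near-separation needs d of about 2 or more, or a marked floor in never-users.

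**Room left for physiology.** Suppose three independent physiological features each differ by d = 0.8. The best linear combination has D² equal to the sum of the squared differences.
- Physiology alone: D² = 3 × 0.64 = 1.92, AUC = Φ(√1.92/√2) = Φ(0.98) = 0.84.
- With craving d = 2.5: D² = 6.25 + 1.92 = 8.17, AUC = Φ(2.02) = 0.98, against 0.96 for craving alone.
- With craving d = 0.8: D² = 0.64 + 1.92 = 2.56, AUC = Φ(1.13) = 0.87, against 0.71 for craving alone.

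Even with no estimation error, strong craving leaves physiology about 0.02 of AUC to add. Moderate craving leaves about 0.16.

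**Simulation at the planned size.** There were 20 versus 20 participants, one craving score and eight independent physiological features, three of which carried d = 0 or d = 0.8. The penalty was chosen by 5-fold cross-validation, the AUC was taken from the same folds at the chosen penalty, and each row has 60 data sets. In the floor scenario 85% of nonvapers score 0 and the rest score 0 to 15; vapers are normal with mean 45 and SD 28, truncated to 0 to 100. Presence and social presence were left out. Every effect size is an assumption. Selection is the share of the three features kept.

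| Craving | Physiology | Joint AUC | Physiology-only AUC | Selection, joint | Selection, physiology-only |
|---|---|---|---|---|---|
| d = 0.8 | noise | 0.64 | 0.48 | 0.19 | 0.11 |
| d = 0.8 | d = 0.8 | 0.77 | 0.75 | 0.81 | 0.85 |
| d = 1.5 | noise | 0.83 | 0.44 | 0.21 | 0.04 |
| d = 1.5 | d = 0.8 | 0.87 | 0.73 | 0.78 | 0.77 |
| d = 2.5 | noise | 0.95 | 0.48 | 0.38 | 0.11 |
| d = 2.5 | d = 0.8 | 0.96 | 0.75 | 0.72 | 0.85 |
| floor | noise | 0.93 | 0.47 | 0.40 | 0.07 |
| floor | d = 0.8 | 0.96 | 0.76 | 0.79 | 0.84 |

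When physiology goes from noise to informative, the joint AUC rises by 0.13, 0.04, 0.01 and 0.03 down the four craving scenarios. The physiology-only AUC rises by 0.27, 0.29, 0.27 and 0.29. In the two strong-craving scenarios, the selection gap between informative and noise features is 0.34 and 0.39 in the joint model, against 0.74 and 0.77 in the physiology-only model.

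**The case against.** The case against is substantial, and much of it stands.

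- The combined question is posed openly in the Abstract objective and the Secondary Aim. A reader might infer that the LASSO answers a question nobody asked; the documents do not support that.
- The primary mixed ANOVA compares gaze, heart rate and electrodermal measures between groups separately from craving. A reader might infer that a modest physiological difference would be hidden. It would still be tested there, whatever the LASSO selects.
- Coefficients for the biometrics in the joint model are conditional on craving and so bear on added information. Selection still responds to real signal even when craving is strong (0.72 to 0.79 against 0.38 to 0.40 for noise).
- The analysis is labelled exploratory, limited to candidate markers, and promises no AUC.
- The article speaks of regularized analyses in the plural and does not rule out separate predictor blocks. A fuller plan might contain them.

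What does not dispose of the point: the ANOVA works measure by measure, so it says neither how well the biometrics discriminate jointly nor what they add to self-report. Cautious interpretation cannot supply a comparison that is not fitted. The pooled predictor set is stated in the article; it is not a detail left open.

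**Conclusion.** The point holds as a limitation of the stated predictor set. One joint LASSO estimates neither the joint discrimination of the biometrics nor their increment over self-report, and the biomarker aim in the Background and Conclusions needs both. This follows from the design of the model and does not depend on any assumed effect size.

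The practical size does depend on craving. With d of about 2.5 or a floor in never-users, joint AUC is 0.93 to 0.96 whether or not physiology is informative. At d = 0.8 it moves from 0.64 to 0.77 and the masking is much weaker.

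A reader might go further and infer that craving alone nearly separates the groups. It is plausible from the group definitions and the wording of the item, but the article reports no craving mean, SD or effect size. Nonvapers may also use other nicotine: "Participants who use nicotine in non–e-cigarette forms (eg, cigarettes and nicotine pouches) will not be excluded". Nor is it right that the joint model can show nothing about the biometrics, as the selection rates make clear. This is a worthwhile, inexpensive improvement to an exploratory analysis; it does not invalidate the plan.

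**What to change.** In Secondary Analyses, keep the combined LASSO for the question in the Secondary Aim and add two models:

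1. a LASSO on the gaze, heart rate variability and electrodermal features only, named as the model that addresses the biomarker question;
2. a benchmark on craving, presence and social presence only.

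Report the cross-validated performance of all three and the gain of combined over subjective-only. State that the combined model's performance will not be attributed to the VR biometrics alone. If craving is strong the gain will be small even for informative physiology (about 0.02 in the calculation above), so it should be read beside the physiology-only result.

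The cost is two extra exploratory fits on data already being collected, and possibly a lower headline discrimination figure. Data from 7 of the planned 40 participants had been collected by March 2026, so when that status was reported the models could still be specified before most of the data existed.

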## Methods

### Study Design

This study will examine individuals’ psychological, behavioral, and physiological responses to e-cigarette cues in VR among young adults aged 18 to 21 years. We focus on this age range because the transition into early adulthood often brings increased exposure to vaping-related social contexts (eg, college gatherings) [27], and this pilot allows us to first test the paradigm in adults before adapting it for adolescent populations. A between-subjects design is used to compare current e-cigarette users and nonusers, with a within-subject, counterbalanced component to assess 2 cue conditions (with and without social pressure). This mixed-design approach enables testing of cue effects and group differences while controlling for individual variability.

Prior VR nicotine cue reactivity studies have reported medium-to-large effects for the response difference between user and nonuser groups [17,28]. Based on the relevant research and using G*Power 3.1 (Heinrich Heine University Düsseldorf) for a 2 (group: vapers vs nonvapers)×2 (cue condition: social pressure vs no social pressure) mixed design, we powered the study for the group × cue condition interaction (group×cue condition) assuming a medium effect (*f*=0.25; partial η-squared ≈ 0.06; power=0.80). We assumed a within-participant correlation of *r*=0.50 between cue conditions and a nonsphericity correction of *ε*=1.0 (sphericity is not applicable with 2 within-subject levels). This yields a minimum required sample of 34 (n=17 per group). To ensure robustness and account for potential data loss (eg, eye-tracking dropout and physiological artifacts), we plan to recruit 40 participants in total (n=20 vapers and n=20 nonvapers).

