### Ethical Considerations

This study has been approved by the Yale University Human Subjects Committee (2000040783). The study protocol was prospectively registered on the Open Science Framework on November 26, 2025. Although not required for this study type, registration was completed to support transparency and reproducibility.

We have assessed that the study poses no greater than minimal risk to participants. The key ethical issues we considered include breaches of confidentiality and exposing individuals who have never used nicotine-containing e-cigarettes to vaping-related cues.

Under Connecticut law, the legal age to purchase e-cigarettes is 21 years, and it is illegal for anyone to sell, give, or deliver e-cigarettes to individuals below 21 years [53]. As our study recruits young adults aged 18 to 21 years and assesses past substance use behaviors, participants might have to disclose underage substance use behaviors. To ensure data privacy, participants will be assigned unique study identification numbers, and substance use behaviors and physiological data will be kept separate from identifying information. The consent form will clearly state these risks and list the protections available to participants. Participants will also be reminded that they can withdraw from the study at any time and have their records removed without penalty.

For the collected data, all information will be stored on secure Yale-managed encrypted servers accessible only to approved study personnel. Identifiable information will be stored separately from study data and linked through coded participant IDs. Physiological data collected in this study include eye-gaze direction, HR, and EDA. Eye tracking records only gaze direction toward predefined regions of interest and do not capture images, video, or pupil size. HR and EDA are collected as physiological signals that do not contain identifiable biological information. Study data will be retained for a minimum of 5 years following study completion in accordance with institutional policy. Deidentified, aggregate-level data may be shared for scientific purposes upon reasonable request and institutional review board approval.

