### Limitations

This study protocol has several limitations. First, vaping initiation and cessation intentions will be assessed through self-report questionnaires at a single time point (at the time of the study) rather than via a longitudinal follow-up, which would allow validation of participants’ future vaping behaviors. The study is designed as an observational laboratory protocol and does not include follow-up, as it is not intended to influence or assess behavioral change over time. Accordingly, self-reported susceptibility and intention are established proxies for early indicators of nicotine use risk [42,62,63], and this study paradigm can inform future work validating VR-based biomarkers through longitudinal designs. Second, our VR stimuli focus primarily on visual immersion and do not incorporate multisensory elements such as olfactory cues, which are known to play an important role in e-cigarette use and craving [15]. Future work could expand to multisensory designs for greater ecological validity. Third, recruitment is limited to young adults aged 18‐21 years in the New Haven, Connecticut area, a sample likely to be predominantly university students and not fully representative of broader younger populations at risk. Fourth, one of the primary outcome measures, eye gaze direction, will be disclosed to participants before the VR session, which may influence natural viewing patterns. Additionally, both eye-tracking and physiological signals (HR and EDA) are susceptible to noise and motion artifacts [24], particularly in room-scale VR where participants move freely. We will mitigate these issues through standard preprocessing procedures and noise correction, but residual artifacts may still affect data quality. Despite these limitations, this study provides an important step in establishing the feasibility of VR-based psychophysiological assessment for nicotine use and risk prediction, laying the groundwork for larger-scale and more representative trials.

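### The 15% missing-data rule removes whole participants rather than the failed signal, so as written it discards valid data in the secondary analyses; whether it reaches the primary ANOVA is left open

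*Protocol article*

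**What the plan says.** The rule appears once, in the preprocessing paragraph of Secondary Analyses: "Participants will be excluded if more than 15% of their physiological data is missing". The same sentence then sets a narrower rule for one channel: "EDA signals will be removed if more than 15% of values are zero or negative". Before either threshold, the paragraph provides for "removal of segments affected by motion artifacts or signal instability"; it does not say whether removed segments count as missing.

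Ethical Considerations defines the data broadly: "Physiological data collected in this study include eye-gaze direction, HR, and EDA". The Primary Aim lists those three signals as outcomes beside craving, sense of presence and social presence. Assessments (Table 2) collects the latter by questionnaire after each cue scene, with the headset off.

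On sample size, Study Design states "we powered the study for the group × cue condition interaction", and concludes "This yields a minimum required sample of 34 (n=17 per group". It recruits 40, naming eye-tracking dropout and physiological artifacts as the reasons for the extra 6, but gives no expected loss rate. Limitations expects noise and motion artifacts in gaze, HR and EDA, "particularly in room-scale VR where participants move freely". The Primary Analyses section contains no exclusion rule.

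**The concern.** A sensor fault is a property of one signal, possibly in one scene. The rule answers it by removing the person. Followed as written, a gaze–craving correlation loses a participant because the pulse signal was bad, although both members of that pair are valid.

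This bites hardest in the correlations with dependence and quit intention (vapers only) and with susceptibility (nonvapers only). Each starts from 20 people, and the minimum of 34 gives them no protection.

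The two halves of the sentence also need reconciling. If an EDA signal removed for poor contact counts as missing, it could itself push the participant past 15%, and the signal-level rule would then have no effect.

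Finally, losses depend on movement and sensor contact. These may relate to arousal or to group, so dropping whole participants could make the retained sample selective. The article gives nothing from which to size that bias.

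**Working it through.** **Inputs.** From Study Design: 2×2 mixed design, f = 0.25, correlation 0.50 between conditions, ε = 1.0, target power 0.80, minimum 34, planned 40. Alpha is not stated; 0.05 two-sided is assumed. Failure rates are not stated; those below are illustrative.

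**1. The plan's own figure.** For the within–between interaction with m = 2 conditions, the noncentrality is λ = f²·N·m/(1 − ρ), with 1 and N − 2 degrees of freedom. At N = 34, λ = 0.0625 × 34 × 2 / 0.5 = 8.5 and power is 0.807. At N = 32 power is 0.781. So 34 is the smallest even N that reaches 0.80, and the stated minimum reproduces. At N = 40 power is 0.869.

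**2. The margin.** 40 − 34 = 6, and 6/40 = 15%. A seventh exclusion leaves 33, with power 0.795. A fourth exclusion in one group leaves 16, below the stated 17.

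**3. How fast whole-participant exclusion uses the margin.** With k units failing independently, each with probability p, the excluded share is 1 − (1 − p)^k. HR and EDA come from one wrist-worn device (Software Development and Apparatus), so k = 2 (headset and wrist device) is a natural case and k = 3 is the high end. At p = 0.10:

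| Failure pattern | Excluded | Expected N of 40 | Power near that N | P(N < 34) |
|---|---|---|---|---|
| All failures coincide | 10% | 36 | 0.830 | 0.10 |
| Headset and wrist device independent | 1 − 0.9² = 19% | 32.4 | 0.781 (N = 32) | 0.66 |
| Three signals independent | 1 − 0.9³ = 27.1% | 29.2 | 0.738 (N = 29) | 0.95 |

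Exclusion passes 15% once per-unit failure exceeds 7.8% (k = 2) or 5.3% (k = 3).

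**4. Signal-level handling at the same 10%.** Each signal keeps an expected 40 × 0.9 = 36, with P(N < 34) = 0.10. The questionnaire outcomes keep all 40 if the questionnaires are complete.

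**5. Within-group correlations.** The critical value is |r| = t/√(t² + n − 2), two-sided 0.05. At n = 20, t = 2.101 and |r| = 0.444. At 10% failure, signal-level handling leaves 20 × 0.9 = 18, where t = 2.120 and |r| = 0.468. Three independent failures leave 20 × 0.729 = 14.6; at n = 15, t = 2.160 and |r| = 0.514.

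**6. The EDA clause.** If the 15% is taken over three equally weighted signals (an assumption; the article defines no denominator), a removed EDA signal makes 1/3 = 33% missing. That exceeds 15% and would trigger the first half of the sentence.

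**The case against.** The strongest reply is about scope. The rule stands between the LASSO predictors and the LASSO tuning step, in a paragraph that ends by calling the analysis exploratory. A LASSO needs a complete feature row per person, so a participant-level rule is ordinary there. A reader might infer that valid primary craving data will be lost and that the study will fall below 34. The article does not support either as a statement of fact: the minimum belongs to the primary interaction, and the rule is not stated for the primary ANOVA. Nor is it ruled out, since no other missingness threshold is given, and Study Design itself ties signal loss to the primary sample size. This part of the objection stands, and the effect on the minimum is therefore conditional.

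A reader might also infer that one failed EDA channel always removes the person. The signal-level clause points the other way for poor contact, because on the opposite reading it would be pointless. That stands too; what remains is a wording conflict, plus EDA lost for other reasons. The denominator is also unsettled: Ethical Considerations counts gaze as physiological, while Assessments and Limitations name it separately. On the narrower usage, gaze loss would not trigger the rule.

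The loss was anticipated by recruiting 6 extra, no failure rate is given, and a small breach costs little: power is 0.795 at 33 and 0.753 at 30. These points limit the size of the problem. They do not answer the main one: outside the LASSO, nothing is gained by dropping a valid gaze–craving pair because of a bad pulse signal.

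**Conclusion.** The point holds for the unit of the rule. As written it discards valid questionnaire data, and valid data from working sensors, in the secondary correlations, and that does not depend on any assumed failure rate. It is also poorly reconciled with the EDA clause beside it.

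The consequence for the minimum of 34 is conditional on two things that the article does not give: whether the rule governs the primary ANOVA, and how often signals fail. If it does govern, an assumed 10% failure per unit excludes between 10% (margin usually holds) and 27% (about 29 left, power about 0.74), with 19% (about 32 left, power about 0.78) when the two devices fail independently. Three independent failures is a high-end scenario. The power figures assume alpha 0.05 and the plan's f and correlation. Bias from selective exclusion is possible but cannot be sized. The change should be made; it does not call the design into question.

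**What to change.** - State which analyses the 15% rule governs and what the percentage is taken over, including whether removed artifact segments count as missing.
- Apply the threshold per signal and per scene, and set only that signal-scene value to missing. This also reconciles it with the EDA clause.
- Keep each participant in every analysis for which they have valid data, including all craving, presence and social-presence analyses.
- Restrict any complete-feature requirement to the LASSO.
- Report usable-data rates per signal by group. This serves the stated feasibility goal and shows whether loss differs between vapers and nonvapers.

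The cost is analysis wording and an N that differs slightly by outcome. Data from only 7 of 40 participants had been collected by March 2026, so the wording can be settled before analysis. A linear mixed model in place of the ANOVA is optional; it would let a participant with one usable scene contribute, but the fix does not depend on it.
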